**Fig. 2 Fig2:**
[figure not shown]
Case study procedure

**Fig. 3 Fig3:**
[figure not shown]
Treatment site of the abdominal muscle fascia trigger point. The blue dots, the rectus abdominis attachment point is located above the pubic symphysis (bilateral); the yellow dots,the intersection of the anterior superior iliac spine with the outer edge of the rectus abdominis (bilateral); the red dots, the anterior superior iliac spine moving inward about 2 cm along a straight line (bilateral)

**Fig. 4 Fig4:**
[figure not shown]
Description of the shockwave instrument. Above is the front view of the shockwave instrument (model: MASTERPULS MP100), and below is the side view of the treatment handle (model: R-SW handpiece)

**Table 2 Tab2:** Details of rESWT intervention

Item	Detail	Description
rESWT rationale	Type of shock wave	Pneumatic ballistic extracorporeal shock wave therapy
	Reasoning for treatment	The best treatment option was selected according to our previous study results and other clinical trials of rESWT for primary dysmenorrhoea
	Extent to which treatment varies	None
Details of rESWT	Number of treatment sites per subject	6
	Names of points used	Attachment point of rectus abdominis above the symphysis pubis (bilateral) (blue dot in Fig. 3)
		Intersection of the anterior superior iliac spine with the outer margin of the rectus abdominis (bilateral) (yellow dot in Fig. 3)
		The anterior superior iliac spine shifts inward by approximately 2 cm along the line (bilateral) (location of the red dot in Fig. 3)
	Shock wave intensity	1.5–2.0 bar
	Shock wave frequency	10–14 Hz
	Number of hits from each site	600 times
	Response sought	None
Treatment regimen	Number of treatment sessions	1 time
	Treatment time	Within 48 h of menstruating
Other components of treatment	Details of other interventions administered to the rESWT group	None
	Setting and context of the treatment	Hospital rehabilitation section, outpatient department
Background of practitioner	Profile of the therapist	Specialist in rehabilitation medicine or a resident of more than 1 year under the guidance of the specialist in rehabilitation medicine
Control or comparator	Rationale for the control or comparator in the context of the research question	As a placebo control, a non-energetic sham rESWT was used

### MRI scanning procedure

The Siemens 3.0 T Magnetom Verio MRI system (Siemens Medical, Erlangen, Germany) with 32-channel head coil will be used to obtain MRI data on pain relief after rESWT treatment at the Department of Radiology, Zhongshan-Xuhui Hospital, Fudan University, Shanghai, China. To avoid head movement, foam pads will be used to fix the participants’ heads. The fMRI data will be acquired with a single-shot gradient recalled echo planar imaging sequence with the following parameters: repetition time (TR)/echo time (TE) = 2530 ms/2.98 ms, flip angle = 7, field of view (FOV) = 256 mm × 256 mm and slice thickness = 1 mm. To obtain the resting fMRI data, a whole-brain blood oxygenation level-dependent (BOLD) pulse sequence (TR/TE = 2000/30 ms, flip angle = 90, FOV = 192 mm × 192 mm, voxel size = 3.0 × 3.0 × 5.0 mm, slice thickness = 1 mm and 28 slices) will be used.

### Outcome measurements

#### Primary outcomes

##### SF-MPQ

The primary outcome will be the change in the short form of the McGill Pain Questionnaire (SF-MPQ) score (Table 1). The SF-MPQ is a scale composed of a pain rating index, a visual analogue scale and existing pain intensity to measure pain intensity. The pain rating index consists of 11 sensory and 4 emotional pain descriptors, all of which are rated from 0 to 3 points to indicate the different degrees of no, mild, medium, or severe pain, respectively. This index is a sensitive and reliable pain evaluation method widely used in the assessment of dysmenorrhoea [18].

##### CMSS

The menstrual pain symptoms of participants will be integrally evaluated by the Cox Menstrual Symptom Scale (CMSS), which consists of 18 items or symptoms, including cramps, nausea, vomiting, loss of appetite, headaches, backaches, leg aches, dizziness, weakness, diarrhoea, facial blemishes, abdominal pain, flushing, sleeplessness, general aching, depression, irritability, and nervousness [19]. The scale is mainly used to evaluate the severity and duration of menstrual pain symptoms. All items use a five-level scoring method ranging from 0 to 4 points. The choices for pain severity include painless, mild pain, moderate pain, severe pain, and very serious pain. Patients can evaluate the duration of their pain as 0 h, less than 3 h, 3–7 h, 7–24 h and more than 24 h. The CMSS will be used before and after rESWT treatment.

#### Secondary outcomes

##### Zung SAS

The Self-rating Anxiety Scale (SAS) will be used to measure anxiety-related symptoms in PDM since dysmenorrhoea is often accompanied by emotional change. It is a self-administered questionnaire, with each response using a four-point scale from 0 (none of the time) to 4 (most of the time). A total score above 40 indicates a clinically relevant anxiety disorder [20]. The SAS will be utilised before and after rESWT treatment (Table 1).

##### SDS

The Self-rating Depression Scale (SDS) is a scale used to evaluate changes in terms of depression [20]. In this trial, participants will fill out 20 items based on their actual experience over the past week. The total score for this scale ranges from 20 to 80, with a score above 40 indicating depressive symptoms. This scale will be employed before and after rESWT treatment (Table 1).

### Sample size calculation

The smallest significant differences in clinical treatment are considered to assess the effects of different treatments. SAS 9.4 software was used to design the two groups with better efficacy. The optimal value was defined as 15%. According to previous research results, the effectiveness proportion of shock wave treatment for primary dysmenorrhea is known to be 0.8 [9, 10]. The control group for this experiment was the sham shock wave treatment group. Through previous practice observation, we determined the effectiveness of the control group proportion to be 0.45. The estimated sample size was 30 individuals (15 in each group) to meet the 80% statistical value [21] and the 5% significance level. Considering a 20% drop-out rate, the sample size was finally determined to be 36 participants (18 per group).

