### Statistical analysis

Clinical and MRI outcomes will be obtained in this study. Among these outcomes, results from participants for both MRI scans and two clinical evaluations will be included in the results analysis; otherwise they will be considered data from drop-outs. Note that all participants in the experiment will receive our instructions before participating.

Statistical analysis of the clinical outcomes will be accomplished using the SPSS 22.0 statistical software. All tests will be bilateral, and *p* < 0.05 will be considered statistically significant.

Demographic characteristics and baseline information for all participants will be analysed statistically. For continuous data, independent sample *t* tests or Wilcoxon rank sum tests will be applied for analysis with data represented as mean ± standard deviation. If dichotomous data occur, we will use the chi-square test or the Friedman test and represent the data as percentiles.

For post-test results, the paired *t* test or Wilcoxon signed rank test will be employed for continuous data within the group. Conversely, the chi-square test or Fisher’s exact test will be applied for two-part data to compare the differences before and after treatment. For different intervention methods, independent sample *t* tests will be conducted to identify whether the intervention methods show differences for the relief of PDM.

The statistical comparison of MRI data will be conducted in different ways. With the use of the 3.0 T Siemens Magnetom Verio MRI system, each subject will produce two resting state scans. The data processing assistant for resting state fMRI (DPARSF 4.4) software package will be used to process MRI data on the MATLAB 2015b platform and obtain the ALFF values. The mean value of the amplitude of all frequency points within 0.01–0.08 Hz will be calculated; that is, the intensity of the BOLD signal changes will be calculated to obtain the brain map of the statistical parameter of amplitude, which will be used to describe the spontaneous activity of the voxel [23]. SPM12 software will be employed to perform two-sample *t* tests on the two groups of statistical brain maps. The final results will be superimposed on standard avg152 T1 images for display. Finally, the statistical difference of low-frequency amplitudes in the resting state between the two groups will be obtained, and *p* < 0.05 will be considered to indicate a significant statistical difference.

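### The 80% power claim belongs to an undefined effectiveness proportion, not to the t tests planned for the two score-based primary outcomes, and 15 per group does not deliver it for that proportion either

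*Protocol article*

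**What the plan says.** In the protocol article, Sample size calculation, the active-arm assumption is that "the effectiveness proportion of shock wave treatment for primary dysmenorrhea is known to be 0.8". For sham it says "The control group for this experiment was the sham shock wave treatment group. Through previous practice observation, we determined the effectiveness of the control group" as a proportion, the value being 0.45. A further value is given without explanation of its role: "The optimal value was defined as 15" per cent. The result is "The estimated sample size was 30 individuals (15 in each group) to meet the 80% statistical value" and "the 5% significance level", raised to 36 (18 per group) for 20% drop-out.

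Under Primary outcomes, the SF-MPQ subsection says "The primary outcome will be the change in the short form of the McGill Pain Questionnaire (SF-MPQ) score". The CMSS stands under the same heading, and the abstract names both as main indicators. The secondary outcomes are the SAS, the SDS and fMRI changes.

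Under Statistical analysis, tests are two-sided at 5%, and independent-sample t tests "will be conducted to identify whether the intervention methods show differences for the relief of PDM". Chi-square and Fisher tests appear for two-category data after treatment, but to compare before with after. The other provision for dichotomous data is in the paragraph on demographic and baseline information.

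**The concern.** The hypothesis that was sized is a between-arm difference in a response rate. It has no outcome definition and no planned between-arm test. The hypothesis that will be tested is a between-arm difference in scores. It has no stated difference, SD or power. The same gap applies to SF-MPQ and to CMSS.

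Two things are at stake. A reader cannot tell what difference on either primary outcome the trial can detect, so a non-significant t test could be taken as a negative result from a trial with 80% power. And because effective is undefined while the sizing rests on it, the text leaves room for a response cut-off set later to be presented as the endpoint on which the trial was sized.

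**Working it through.** **Inputs from the protocol.** Proportions 0.80 and 0.45 (difference 0.35); 80% power; two-sided 5%; 15 per group evaluable, 18 per group randomised; 20% loss. The protocol gives no difference and no SD for SF-MPQ or CMSS, so effects on the scores are expressed in SD units.

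**1. The plan's own figure.** The pooled-variance formula for two proportions, with mean proportion 0.625, is

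n per group = [1.960 × √(2 × 0.625 × 0.375) + 0.842 × √(0.80 × 0.20 + 0.45 × 0.55)]² / 0.35² = (1.342 + 0.537)² / 0.1225 = 28.8, so 29 per group.

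The unpooled form gives 27, the arcsine form 29 and the continuity-corrected form 35. One-sided versions give 21 to 29. None gives 15 per group. A figure near 30 appears if the per-group number (29 to 30) is read as the total. A figure of 15 per group also appears if the unexplained 15% is added to the difference (0.50, pooled variance: 14.1 to 14.7). The protocol does not say that either was done.

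**2. Power for the stated proportions.** This comes from summing the two binomial distributions over all tables with p < 0.05.

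| Per group | Normal approximation | Exact, chi-square | Exact, Fisher |
|---|---|---|---|
| 15 | 51% | 52% | 34% |
| 18 | 59% | 63% | 48% |

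**3. What the planned test can detect.** For a two-sided t test with n per group and standardised difference d, power comes from the noncentral t distribution with 2n − 2 degrees of freedom and noncentrality d × √(n/2). With 20% loss, 36 × 0.8 = 28.8 women remain, roughly 14 per group.

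| Evaluable per group | d for 80% power, 5% | d for 80% power, 2.5% | Power at 0.5 SD, 5% | Power at 0.8 SD, 5% |
|---|---|---|---|---|
| 14 | 1.10 | 1.23 | 25% | 53% |
| 15 | 1.06 | 1.18 | 26% | 56% |
| 18 (no loss) | 0.96 | 1.07 | 31% | 65% |

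The 2.5% column assumes that alpha is split equally over SF-MPQ and CMSS. The protocol states no such split.

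**4. Can the two be linked?** Only by assumption. If effective meant passing a cut-off on a normally distributed score with equal SDs, 0.80 against 0.45 would be a shift of 0.842 + 0.126 = 0.967 SD. For that shift, t-test power at 5% is 69% with 14 per group, 72.5% with 15 and 80.5% with 18. Nothing in the protocol says that effective was defined in this way.

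**The case against.** **The proportion can be translated, and the design then meets its target.** On the normal-shift assumption, 18 per group has about 80% power for the t test. A reader might infer from this that the 36 women do better on the real primary outcome than the sizing paragraph suggests. The protocol does not support that: it never ties effective to a score cut-off, and the 80% needs all 36 women to be evaluable, whereas the plan expects 20% loss and treats anyone without both scans and both clinical evaluations as a drop-out. The opposite inference, that the design has failed or that 36 women can tell us nothing about the scores, is not supported either. The trial has reasonable power for differences near 1 SD. What is missing is a power statement that belongs to the test.

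**Tests for binary data are planned.** They are, but the post-treatment provision is worded as before versus after, and no effectiveness rate is named. It does not supply the between-arm comparison that was sized. It is also fair to note that the t-test sentence names no variable. That it refers to the scores follows from the outcomes listed.

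**No responder analysis is planned, so a later cut-off is conjecture.** Correct. A reader might infer that one is intended, and the protocol does not say so. The point is only that the wording leaves room for it.

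**The trial calls itself exploratory, and a separate analysis plan may say more.** The Discussion does use that word, which argues for a proportionate correction. But the 80% claim is made, and the abstract says the main results will be used to assess efficacy. The sizing basis, the primary outcomes and the between-arm test are all stated in this document and do not match, so the point does not rest on an omission.

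**Conclusion.** The point holds. The only power statement in the protocol concerns an undefined proportion that is neither an outcome nor compared between arms, so it does not apply to the t tests on SF-MPQ change and CMSS. It is also wrong on its own terms: 0.80 against 0.45 needs about 29 per group, and 15 gives about 52% power (63% at 18) by exact chi-square.

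For the planned test, 80% power requires about 1.06 SD with 15 evaluable per group, 0.96 SD with 18 and 1.10 SD with 14. These figures assume equal SDs, approximately normal scores and an unadjusted two-sided 5% for each outcome. No conversion to points is possible from the protocol: it gives no SD, and it describes the SF-MPQ as a pain rating index, a visual analogue scale and existing pain intensity without saying which component or total is primary. This is a defect in the stated justification of the sample size, not proof that the t-test comparison is unworkable.

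**What to change.** Keep 36 as the fixed number and rewrite the paragraph openly:

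- Withdraw the 80% claim for the proportion. Say that 15 per group does not reach it for 0.80 against 0.45, so that the error is corrected and not just deleted.
- State what the planned test can detect. Suggested text: With 15 evaluable women per group, a two-sided 5% t test has 80% power for a between-group difference of about 1.06 SD (0.96 SD with 18 if nobody is lost; 1.10 SD with 14, about what 20% loss leaves) and about 56% power for 0.8 SD with 15.
- Say that this applies to each of SF-MPQ and CMSS at an unadjusted 5%. If alpha is to be split equally, give 1.18 SD (15 per group) and 1.07 SD (18) instead.
- Name the SF-MPQ component or total that is primary. Convert to points only if the sponsor holds an SD for that measure.
- State that no responder proportion is confirmatory.

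This describes what a fixed number can detect; it does not justify that number after the fact, and the text should say so. The cost is a text change, one recalculation and a less favourable published figure. No extra patients or assessments are needed.

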### Design

This study will be a randomised, assessor- and statistician-blinded, placebo-controlled trial. A total of 36 subjects with PDM who meet the guidelines of the Society of Obstetricians and Gynaecologists of Canada for the diagnosis of PDM will be recruited and randomly assigned to a shock wave group or a sham shock wave group at a 1:1 ratio. Table 1 lists the recruitment process, intervention methods and evaluation, and Fig. 1 depicts the experimental flow chart. The Standard Protocol Items: Recommendations for Interventional Trials (SPIRIT) 2013 checklist is attached as Additional file 1. This study commenced in January 2019 at the Zhongshan-Xuhui Hospital, Fudan University, Shanghai, China.

**Table 1 Tab1:** Study design schedule

Period	Screening	MRI scan	Treatment	MRI scan	Close-out
Menstrual cycle	0 month	1 month	1 month	1 month	1 month
Inclusion and exclusion criteria	√				
Informed consent	√				
Physical examination	√				
Medical history	√				
Comorbidities	√				
Pelvic MRI	√				
Allocation			√		
SF-MPQ		√		√	
CMSS		√		√	
SAS and SDS		√		√	
Patient compliance					√
Reasons for dropout or withdrawals					√
Adverse events					√
Safety evaluation					√

*CMSS* COX Menstrual Symptom Scale, *MRI* magnetic resonance imaging, *SAS* Zung Self-rating Anxiety Scale, *SDS* Self-rating Depression Scale, *SF-MPQ* Short form of the McGill Pain Questionnaire

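### The sample size claims 80% power with 15 per group for effectiveness of 0.80 versus 0.45, but those inputs need 29 per group; 15 per group gives about 51%.

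*Protocol article*

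**What the plan says.** All inputs are in the article.

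- Sample size calculation, shock wave group: "the effectiveness proportion of shock wave treatment for primary dysmenorrhea is known to be 0.8".
- Same section, sham group: "we determined the effectiveness of the control group proportion to be 0.45".
- Same section, a percentage whose role is not explained: "The optimal value was defined as 15" (per cent).
- Same section, result: "The estimated sample size was 30 individuals (15 in each group) to meet the 80% statistical value [21] and the 5% significance level". A 20% drop-out allowance then raises the total to 36, or 18 per group.
- Design: participants are "randomly assigned to a shock wave group or a sham shock wave group at a 1:1 ratio".
- Statistical analysis: "All tests will be bilateral, and *p* < 0.05 will be considered statistically significant".

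The first objective is efficacy against placebo; no non-inferiority aim appears anywhere. The primary outcomes are the SF-MPQ and CMSS scores, and the Statistical analysis section compares the two interventions by independent-sample t tests.

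**The concern.** A 35-point difference between two proportions cannot normally be detected with 80% power from 15 participants per arm, so the stated result looks too small for its own inputs. The 80% is the only power statement in the article. If it is wrong, readers will judge the result against a sensitivity that the calculation does not support, and a non-significant finding could be taken as evidence that the treatment does not work.

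**Working it through.** **Inputs.** p1 = 0.80 and p2 = 0.45 (Sample size calculation); difference 0.35; 5% significance and 80%, read as power (same section); two-sided (Statistical analysis); 1:1 allocation (Design). Mean proportion (0.80 + 0.45)/2 = 0.625.

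**Step 1: required size, null hypothesis of no difference.**

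n per group = [1.96·√(2·0.625·0.375) + 0.8416·√(0.80·0.20 + 0.45·0.55)]² / 0.35²
= [1.96·√0.46875 + 0.8416·√0.4075]² / 0.1225 = 28.8, so **29 per group (58 in total)**.

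The choice of formula does not bring this near 15:

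- unpooled variance: 26.1, so 27
- arcsine: 28.4, so 29
- pooled variance in both terms: 30.03, so 31
- continuity-corrected: 35
- one-sided 5%, which would contradict the article: still 23 with the formula above (22.6), or 21 unpooled (20.6)

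**Step 2: power at the sizes in the plan.**

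Power = Φ{[0.35 − 1.96·√(0.46875/n)] / √(0.4075/n)}

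At n = 15: (0.35 − 0.3465)/0.1648 = 0.021, and Φ(0.021) = 0.509.

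| Evaluable per group | Normal approximation | Exact, chi-square | Exact, Fisher |
|---|---|---|---|
| 14 (18 × 0.8 = 14.4) | 48% | not run | not run |
| 15 | 51% | 52% | 34% |
| 18 | 59% | 63% | 48% |
| 29 | 80% | 80% | 71% |

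**Step 3: what 15 per group can detect.** For 0.90 versus 0.45 the mean proportion is 0.675. Power = Φ{[0.45 − 1.96·√(0.43875/15)] / √(0.3375/15)} = Φ(0.1148/0.15) = Φ(0.765) = 78%; exact enumeration of the chi-square test gives 81%. So 80% power at 15 per group needs roughly 0.90 versus 0.45, a 45-point difference.

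**Step 4: can the 15% account for the figure?** Its role is not stated, so each line rests on an assumed meaning.

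- Superiority margin to be exceeded: (1.96 + 0.8416)²·0.4075/(0.35 − 0.15)² = 7.849·0.4075/0.04 = 80 per group (89 to 92 with pooled-variance forms). Power at 15 per group is about 19% to 23%.
- Smallest difference worth detecting, 0.60 versus 0.45: 173 per group; power at 15 per group is about 12%.
- Added to the difference, so that the null is shock wave 15 points worse than sham: 7.849·0.46875/0.50² = 14.7, so 15. This is a non-inferiority null, which does not fit an efficacy aim against sham.

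**Step 5: another route to 15.** A one-sample formula (0.80 against a fixed 0.45) gives [1.96·√0.2475 + 0.8416·√0.16]²/0.1225 = 14.05, so 15 per group, without using the 15%. It treats the sham rate as known, which does not fit a two-group trial.

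**The case against.** The strongest objection is that the calculation is not about the primary analysis. The primary outcomes are scores compared by t tests, and the article gives neither a responder definition nor a primary between-group responder comparison. This stands, and it limits the consequence. A reader might infer that the trial has an even chance of missing a real effect. The documents do not support that. At 15 per group a two-sided t test has 80% power for a standardised difference of about 1.06, but no standard deviation or expected score difference is given, so the power for the scores cannot be determined and may lie above or below 51%. The objection does not rescue the 80%, which is claimed for proportions and fails on those terms.

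A reader might also infer that the 15 must come from a non-inferiority calculation. That does not follow: a one-sample formula reaches the same number, and the total of 30 is also close to the correct size of one group. The article does not say how the figure was obtained.

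Finally, the limitations part of the Discussion calls the trial exploratory and looks ahead to larger ones. This softens the risk that a null result is misread, but leaves the power statement uncorrected. Nor can condensation into an article explain the gap, because every input to the calculation is printed.

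**Conclusion.** Wrong as written. For 0.80 versus 0.45 at two-sided 5%, 80% power needs 29 per group, about twice the stated 15. Power is about 51% at 15 per group, about 59% at 18, and about 48% at the 14 per group that the stated drop-out rate leaves; Fisher's exact test would give less. These figures rest only on inputs printed in the article and on reading the 80% as power. The figures for the 15% value are conditional on an assumed meaning, but no meaning compatible with showing better efficacy than sham brings the requirement down to 15. The conclusion is confined to a binary effectiveness comparison; it does not establish the power of the SF-MPQ and CMSS comparisons.

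**What to change.** In the Sample size calculation section, replace the 80% statement with wording such as:

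> For effectiveness proportions of 0.80 versus 0.45 (two-sided 5%), power is about 48–51% with 14–15 evaluable participants per group and about 59% if all 18 per group are evaluable. With 15 per group, 80% power requires about 0.90 versus 0.45.

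Name the test behind these figures (normal approximation to the uncorrected chi-square test). In addition:

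- define the 15% and give the power under it, or delete it;
- say that the calculation concerns a binary effectiveness comparison and does not give the power of the planned t tests on SF-MPQ and CMSS scores;
- state in the Methods that the efficacy comparison is exploratory, in line with the Discussion, and report it as an estimate with a 95% confidence interval, so that a non-significant result is not read as evidence of no effect.

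This is a change of text only: no extra participants and no change to the planned tests. The price is a less favourable power statement.
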